### Selection of participants

The electoral roll from the VEC will constitute the sampling frame for never-screened women. The electoral roll will include female Victorian electors born between 1 January 1944 and 31 December 1983, excluding silent and overseas electors. A subset of women will be selected by simple random sampling (using a computer generated random number) and a check will be made against the VCCR CIS database to find a match. Women will be matched on name, address and date of birth and if no match is found, they are eligible for inclusion as never-screened women. If insufficient eligible women are found in the first random subset, another will be selected and the process repeated.

Under-screened women will be identified directly from the VCCR CIS database after excluding women whose last Pap test was <5 years and ≥15 years ago, age <30 years or 70+ years, who have a prior history of cancer, hysterectomy, are deceased, or whose follow-up has ceased. A subset of women will then be selected by simple random sampling (using a computer generated random number) and further considered for: completeness of mailing address, or a change of address, most recent Pap test showing no high-grade abnormality and having not recently migrated or moved. The two-stage process is necessary because the second stage requires assessing episode level information. At this point, if all the above criteria are met, selected under-screened women are considered eligible. Under-screened women will then be grouped into strata (5 years, 6 years, 7 years, 8 years, 9 years, and 10–14 years since last Pap) with approximately equal numbers in each stratum.

### Randomisation

Selected women will be randomly allocated to the two arms of the trial in a 7:1 (HPV self-sampling: current practice) ratio as per a computer generated randomisation schedule stratified by screening history and time since last Pap test (for under-screened only) within blocks or batches of fixed size. The batches will ensure a close balance of numbers in each arm at any time during the trial and will enable us to regulate the administrative work flow as well as the work flow in the laboratory. This will also enable us to monitor participation and contain expenditure if the response is higher than anticipated.

The study ID and no other information will be used for the randomisation. The nature of the intervention and the randomization ratio precludes masking of participants and other study staff, including the data analyst.

### Data plan

#### Data collection

There are a number of ways in which participant information will be returned and collected. Women can post back their pathology information form, call the telephone centre and update details, or return the completed kit (with the form), or staff at VCCR process the return to sender generated during mailout. The data flow will go through several checkpoints of information matching and validation prior to entry, amendment of details or sample processing. Additionally, women in the self-sampling arm will return the questionnaire by post. These questionnaires will be anonymous, therefore when they are returned they cannot be linked to a specific woman.

#### Data analysis

Within each stratum (never- and under-screened) the proportion of women in each arm participating (i.e. primary outcome) will be calculated as will the absolute difference in the proportion of participation between the HPV self-sampling and current practice arms and the corresponding 95% confidence interval and two-sided p-value. An intention-to-treat approach will be used for the analysis, with women who subsequently report they are adequately screened, are pregnant, or have had a hysterectomy, or return to sender, analysed within the arm to which they were randomised. We will also calculate adjusted participation proportions, in which women who report that they are pregnant, have had a hysterectomy, or that they are adequately screened, or return to sender, are removed from the denominators. Participation will be also be reported by age, socio-economic status (SES), cultural background, Indigenous status and time since last Pap test (for under-screened only) within each screening group and trial arm status. SES status classification is an area level variable assigned to women according to their postcode of residence based on the ABS Index of Relative Socioeconomic Disadvantage (ABS 2008) which is derived from Census information. Additionally, the distribution of age and SES will be compared between women who participate and those who don’t within each screening group and trial arm. Estimates and 95% confidence intervals of the proportion of women having appropriate further investigation (i.e. secondary outcome) in the overall and sub-groups of positive HPV test for each screening group will also be calculated. The responses to the different items (i.e. items within the themes: psycho-social, feasibility and practical issues) of the self-sampling follow-up questionnaire will be summarised and reported as the total number and proportion. We will also report the reasons for not returning a self-sampling kit.

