### Primary objective

To determine whether offering home-based HPV self-sampling increases participation in cervical screening, overall and separately for never- and under-screened women when compared to current practice of a reminder letter to attend for a Pap test.

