**Figure 1 F1:**
[figure not shown]
RCT design overview and clinical management for both never- and under-screened women.

To determine which women have no history of a previous Pap smear on the Victorian Cervical Cytology Registry (VCCR) and are thus presumably never-screened, we will link the VCCR to the enrolment information on the Victorian Electoral Commission (VEC). Registration to vote is compulsory in Australia and use of the electoral roll for specific public health programs, such as cancer screening, is permitted under legislation
[30]. Women whose last recorded Pap test was between five and fifteen years ago will be defined as under-screened and identified using the VCCR database only. Under-screened women will be further stratified by years since last Pap test (i.e. 5 years, 6 years, 7 years, 8 years, 9 years, and 10–14 years), with equal numbers in each stratum. Women with a screening history whose last contact with VCCR was 15 years ago or more will probably be difficult to contact given their likelihood of having changed address. In previous VCCR studies of reminder letters, 35% of letters to women whose last Pap test was 15 years ago were “returned to sender”
[11]. Within each stratum, women will be randomly allocated in a 7:1 randomization ratio to the intervention (HPV self-sampling) arm and the current practice arm respectively. The unequal allocation ratio is to ensure there is an adequate sample size in the HPV self-sampling arm to estimate precisely the proportion of women who have a positive HPV test who undergo appropriate further investigation.

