### Ethics

The study was approved by the Human Research Ethics Committee (HREC) of the Victorian Department of Health. Informed consent has been waived for the study because it is primarily a trial of participation in screening, and we wish the results to be directly translatable to the current screening program. Asking women to consent to a trial of participation would potentially invalidate such results. However, women are otherwise fully informed about the testing and subsequent follow-up and once a woman returns the kit with a pathology information form it will represent her consent to test her sample and undergo further appropriate management and use of data. Correspondence sent to women includes a clear statement indicating the process under which VCCR obtained addresses from the electoral roll and participant information form includes statements about privacy of information. Additional information on how the data collected will be stored and utilized in the study is detailed in the brochure sent with the kit or the reminder letter. Provision has been offered for women to opt-off the study. VCCR will inform VEC of women who opt-off and who do not want to be contacted for health screening purposes in future. All materials were revised following focus groups and amended materials submitted for consideration by HREC.

A Data Safety Monitoring Board (DSMB) has been appointed for the duration of the study. The DSMB will be responsible for the review of the primary outcome data. The DSMB will be provided with the full outcome data at six and twelve months post mail-out of the invitation letter. Following review of the data, the DSMB will report back to the Principal investigator with written details of any identified issues and/or recommendations. An interim analysis will also be performed on the primary end point when 50% of the mail-outs have occurred (anticipated to take place around the 3^rd^ month post initial contact). The DSMB could halt or extend the study based on the primary end points. They will also provide clinical advice on detected high-risk HPV where a woman is non-compliant with follow-up, and assess VCCR compliance of follow-up reminders based on participants becoming part of the routine screening program.

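### The pooled under-screened result reflects a time-since-Pap mix set by design, and no estimate weighted to the registry population is described

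*Protocol article*

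**What the plan says.** Trial design subdivides under-screened women by years since last Pap test: "5 years, 6 years, 7 years, 8 years, 9 years, and 10–14 years), with equal numbers in each stratum". Selection of participants repeats the rule, "with approximately equal numbers in each stratum", but describes the draw as follows: "A subset of women will then be selected by simple random sampling". Randomisation is 7:1 within strata of screening history and, for under-screened women, time since last Pap test.

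Data analysis defines the primary estimate: "Within each stratum (never- and under-screened) the proportion of women in each arm participating (i.e. primary outcome) will be calculated", followed by the absolute difference between arms with a 95% confidence interval and a two-sided p-value. The strata named there are the two screening groups, not the six time-since-Pap strata. The same section also plans to report participation by time since last Pap test within each arm.

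The Primary objective asks for the effect "overall and separately for never- and under-screened women". Data analysis describes the primary comparison only within each screening group. Sample size fixes the groups at 8,000 women each.

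The Rationale says that local trials are needed to estimate the likely effect and cost-effectiveness in a given country. Ethics, in justifying the waiver of consent, says "we wish the results to be directly translatable to the current screening program".

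**The concern.** Each of the six strata supplies one sixth of the under-screened sample, whatever its share of the registry. One stratum spans five years and the others one year each, so equal registry sizes would be a coincidence. The stratifying variable is also a strong predictor of the outcome. A pooled proportion over such a sample therefore answers a question about a mix that the design created.

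This matters because the trial is justified by the need for a local figure that can inform the programme. If the pooled under-screened proportion is read as expected uptake among the registry's under-screened women, it may be off by a material fraction of its value. The same holds for the pooled difference if the effect varies with time since last Pap test. An overall figure has a further layer, because the equal split between never- and under-screened women is also a design choice.

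The sampling text adds a smaller difficulty. A simple random sample that is then grouped would not normally give equal strata. The selection probabilities, and so the weights, depend on which description is followed.

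**Working it through.** **1. The plan's own figures.** These reproduce, so no stated number is wrong.
- Follow-up precision: 7,000 × 0.20 × 0.10 = 140 women, and 1.96 × √(0.9 × 0.1/140) = 4.97 points.
- Table 2: the pooled-variance test of two proportions with continuity correction (1/n1 + 1/n2)/2 gives 100, 100, 94.0, 94.8, 86.9 and 80.2%, against 100, 100, 94, 95, 87 and 80% printed.

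**2. Inputs.**
- Sample share: 1/6 per stratum (Trial design).
- Control response: 10% at 6 years, 2% at 10 and 0.4% at 15 (Sample size). Background ties the 0.4% to more than fifteen years, so that anchor is loose.
- Registry stratum sizes: not in the document. Assumption: yearly counts are flat or fall by a constant 5 to 25% per year since last Pap test.

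**3. Stratum rates (log-linear).** r(t) = 0.10 × (0.02/0.10)^((t−6)/4) up to 10 years, then 0.02 × (0.004/0.02)^((t−10)/5). This gives 14.95, 10.00, 6.69, 4.47 and 2.99% for years 5 to 9. For 10–14 years it gives 1.16% on average with flat counts. The 5-year value is an extrapolation beyond the pilot figures.

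**4. Design mix against registry mix.**
- Design mix: (14.95 + 10.00 + 6.69 + 4.47 + 2.99 + 1.16)/6 = 6.71%.
- Registry mix, flat counts (10–14 years holds 5 of 10 years, 50%): 0.1 × 39.10 + 0.5 × 1.16 = 4.49%.

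| Yearly fall in counts | 10–14 share | Design mix | Registry mix | 6Σw² |
|---|---|---|---|---|
| 0% | 50.0% | 6.71% | 4.49% | 1.80 |
| 5% | 43.6% | 6.72% | 5.10% | 1.53 |
| 10% | 37.1% | 6.72% | 5.77% | 1.31 |
| 15% | 30.7% | 6.73% | 6.48% | 1.17 |
| 20% | 24.7% | 6.74% | 7.22% | 1.11 |
| 25% | 19.2% | 6.75% | 7.96% | 1.13 |

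With flat counts, linear interpolation gives 6.9% against 4.7%. Capping the 5-year rate at 10% gives 5.9% against 4.0%. If the one-year strata are equal and the 10–14 share is 30, 40, 50 or 60%, the registry value is 5.8, 5.2, 4.5 or 3.8%, and 6Σw² runs from 1.13 to 2.35.

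**5. The arm difference.** With a constant participation ratio of 2, the difference equals the control rate, so it moves by the same amount (6.7 against 4.5 points, flat counts). With a constant difference it does not move.

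**6. Stratifying the test.** Mantel-Haenszel risk-difference weights are n1n2/N = (1/8)(7/8)N per stratum, proportional to N, so the estimate is essentially the crude difference. With equal rates in both arms, the unstratified SE, √(p1q1/1000 + p2q2/7000), is 0.00846. The stratified SE is 0.00831, a ratio of 1.018. With a ratio of 2 the SEs are 0.00890 and 0.00871 (1.022). Ignoring the strata is slightly conservative, by about 2%.

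**7. Price of weighting.** The factor 6Σw² ranges from about 1.1 to 2.4. It assumes the same binomial variance in every stratum, so it is a rough guide. Using the rates above, the control SE √(6/1000 × Σw²p(1−p)) is 0.78 points for equal weights, 0.62 for flat counts and 0.95 for a 25% yearly fall. As a fraction of the estimate, these are 0.78/6.71 = 12%, 0.62/4.49 = 14% and 0.95/7.96 = 12%. On the rough factor, an effective control sample of 600 would cut power for 5% against 7.4% from 82% to 58% (uncorrected formula). This is a reason to leave the test on the design mix.

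**The case against.** The strongest case against has five parts.

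- **The article is condensed.** It nowhere says that the analysis is unweighted; weights and stratum adjustment may sit in an analysis plan not shown. This stands as a caution. The point rests on the estimate that the article does state and on the equal-numbers rule, not on a missing detail.
- **Results by time since last Pap test are already planned.** With registry counts, any reader could rebuild a programme figure. This stands, and it makes the remedy cheap. The article does not, however, mention the counts or a standardised estimate.
- **Equal sampling is a legitimate design and the comparison is valid.** Both are true. A reader might infer that the primary comparison is biased. It is not, because 7:1 allocation in every stratum balances the arms on time since last Pap test. The issue is which population the pooled figures describe.
- **The direction is unknown.** A reader might infer that the pooled figure overstates programme uptake, since the low-response stratum spans five years. The documents do not support that as a general statement: the discrepancy nearly vanishes if counts fall 15% per year and reverses at 20% or more.
- **Two supporting texts are weak.** The Ethics sentence justifies waiving consent and promises no weighted estimate; the Rationale's call for local estimates is the better support. The sampling wording may simply mean random selection within strata, in which case one clarifying phrase is enough.

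**Conclusion.** The point holds as one of target population and reporting. It does not show a flaw in the randomised comparison. The pooled under-screened participation describes a mix of one sixth per stratum, and so does the difference unless it is constant across strata. Across the assumed yearly declines of 0 to 25%, the pooled control figure lies between 2.2 points above and 1.2 points below the registry-weighted value, on a base of about 6.7%. These magnitudes rest on interpolated pilot rates and assumed stratum sizes, and only the registry counts can settle them. The precision lost by ignoring the strata is trivial and does not carry the point. The overall comparison named in the objective needs stated weights, because its mix is also set by design. The change is worth making, though the trial's main conclusion does not depend on it.

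**What to change.** 1. Record the registry count of eligible women in each of the six time-since-Pap strata at selection.
2. Keep the under-screened test on the trial sample, for power, but stratify it by the six randomisation strata (for example a Mantel-Haenszel risk difference).
3. Beside the planned stratum results, report under-screened participation by arm and the difference, both weighted to the registry counts. Label the pooled figure as the trial-mix estimate.
4. Define the overall comparison in the Primary objective as a stratified combination of never- and under-screened women, and state the weights.
5. Reconcile the simple random draw in Selection of participants with the equal-numbers rule there and in Trial design, for example by stating that sampling is random within each stratum, if that is what is done.

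The cost is six counts from a database that the trial already uses and a few lines of analysis. The downside is a confidence interval that may be wider for the weighted estimate only (variance factor about 1.1 to 2.4 on the rough measure above). The primary test loses nothing.

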### Interventions

Women allocated to the intervention (the HPV self-sampling) arm will be mailed an envelope containing an invitation letter, an information brochure on HPV and cervical cancer entitled *‘The Pap test alternative: the HPV test and cervical cancer’*, and the HPV self-sampling kit. The kit comprises a nylon-tipped flocked swab (Copan Italia, Brescia, Italy) for vaginal sampling enclosed in a plastic tube within a resealable plastic bag; an instruction sheet (both written and pictorial) on ‘*How to take a vaginal sample and how to pack and post the sample’*; a pathology information form; and a postage paid envelope to return the swab and the form. The form will ask for the woman’s country of birth, language spoken at home, whether she identifies as an Aboriginal or Torres Strait Islander woman, hysterectomy status, pregnancy status, Pap screening history, updates of her contact details, and the date she took her sample. Women are able to nominate a GP to receive a copy of the results to enable appropriate referral, follow-up and management should high-risk HPV be detected.

Two to three weeks prior to receiving the kit, women will receive a pre-invitation letter informing them of the upcoming HPV self-sampling kit and the fact that the test is free, and a phone number for calling the Registry (or VCCR) with an option for cancellation of the kit. It will also allow women to call the Registry and update information such as a recent Pap test, correct contact details, hysterectomy, or pregnancy to identify women not eligible for the trial. A multilingual flyer included with the pre-invitation and the invitation letter will state that information is available on the website in the ten most common languages and that an interpreter service is available.

All materials for use in the HPV self-sampling arm were focus group tested. Four focus groups were conducted in August 2013 with Victorian women who would be eligible for the trial, separated by their screening history (never- and under-screened) and age (30–49 and 50–69 years). The main aim was to obtain suggestions for refining all written materials sent with the HPV self-sampling kit with the intent of maximising response to the trial. The overall response to the iPap concept was very positive in the focus groups. The details of the focus group findings will be published elsewhere.

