Women in the HPV self-sampling arm will also receive a questionnaire a few weeks later. This will collect information about their experience with the HPV self-sampling (mostly psycho-social: pain, discomfort, fear, embarrassment; some aspects of feasibility such as ease of use, confidence doing it themselves, adequacy of instructions; and other practical issues such as ease getting an appointment with a GP etc.) and their willingness to participate in HPV self-sampling screening in future. Those who did not return a completed HPV self-sampling kit will be asked to provide reasons for not participating.

Women allocated to the current practice arm will receive either a tailored invitation letter (never-screened) or a standard reminder letter (under-screened) to have a Pap test, as well as a Pap test brochure entitled *‘How Pap tests can help prevent cervical cancer, and the Pap test registry’.* Also included will be a form to collect the similar information as for the HPV self-sampling arm, and a reply paid envelope for return of the form. The requested information will enable analysis of results by cultural background and Indigenous status, and also identify women not currently eligible for screening.

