### Laboratory testing of HPV

All the kits received will be handled, processed and tested by VCS Pathology using the Cobas® 4800 HPV Test (Roche Diagnostics GmBH) according to the manufacturer’s instructions. The test is clinically validated and approved by the FDA. The test specifically identifies high-risk types HPV16 and HPV18 while concurrently detecting 12 other high-risk types (31, 33, 35, 39, 45, 51, 52, 56, 58, 59, 66 and 68) in a single pool at clinically relevant cut offs for detecting infection. This test allows for risk stratification and identification of women who are at the highest risk of cervical cancer (those who are 16/18 positive)
[33] who may need more intensive follow-up. The Cobas® HPV test also has high sensitivity, which is desirable for under-screened women
[34,35]; a Beta-globin internal control for sample adequacy, which will reduce false-negatives; and a lower rate of cross-reactivity with low-risk HPV types, reducing false-positives
[36]. Results are either ‘positive’ for high-risk HPV (HPV 16, HPV 18 and/or other high-risk HPV types) or ‘negative’ for high-risk HPV or unsatisfactory. An ‘unsatisfactory’ result includes specimens damaged in transit; incorrect labelling; non return of the pathology form; inhibition by blood or other substance; or insufficient material to test.

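### Participation by cultural background and Indigenous status would rest on women who chose to return a form, so the denominators are incomplete, tied to the outcome in the kit arm, and selected differently in the Pap arm

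*Protocol article*

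**What the plan says.** All references are to the protocol article.

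- **Planned result (Data analysis).** "Participation will be also be reported by age, socio-economic status (SES), cultural background, Indigenous status and time since last Pap test", the last for under-screened women only, within screening group and arm.
- **Source in the kit arm (Interventions).** The pathology form packed with the kit asks for "country of birth, language spoken at home, whether she identifies as an Aboriginal or Torres Strait Islander woman", along with hysterectomy, pregnancy and screening history.
- **Source in the Pap arm (Interventions).** The letter comes with "a form to collect the similar information as for the HPV self-sampling arm, and a reply paid envelope for return of the form". The article then says: "The requested information will enable analysis of results by cultural background and Indigenous status".
- **Baseline data on never-screened women (Selection of participants).** "Women will be matched on name, address and date of birth and if no match is found, they are eligible for inclusion as never-screened women". Neither variable is among the linkage items.
- **Follow-up questionnaire (Data collection).** "These questionnaires will be anonymous, therefore when they are returned they cannot be linked to a specific woman".
- **Data kept on non-participants (Data security).** Birth year and postcode are retained; their other details are deleted after 12 months.

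**The concern.** A participation proportion in a category needs the number of women mailed in that category. Age, area-level SES and time since last Pap test come from the roll or the registry, so every randomised woman can be classified. Cultural background and Indigenous status are described only as answers on a returned form. A woman who sends nothing back has no value, and at the planned participation that is likely to be most women.

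The proportion that can be calculated is participation among women who returned a form. In the kit arm the form normally travels with the swab, and "non return of the pathology form" is listed under Laboratory testing of HPV as a reason for an unsatisfactory result. Having the variable is therefore closely tied to being a participant. In the Pap arm, posting the form and having a Pap test are separate acts. The two arms condition on different things.

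The Discussion names reducing inequalities as a priority for the screening program. A participation figure for Indigenous women, or for women born overseas, could be taken as evidence of reach when it mostly reflects who posted a form.

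**Working it through.** **The plan's own figures.** Sample size gives 7,000 kit-arm women per screening group, 20% participation and 10% HPV positivity. 7,000 × 0.20 × 0.10 = 140, and 1.96 × √(0.9 × 0.1 / 140) = 4.97 points. Both agree with the stated 140 women and ±5 points. Because the 20% is multiplied by the test's positivity, it serves as the kit-return share. The article gives no figure for the present point.

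**Kit arm.** Let P be the share returning a kit with its form and F the share returning the form without a kit.

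Apparent participation among women of known status = P / (P + F)

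P = 20% is from Sample size. F is not given, so it is an assumption shown over a range. Kit-arm women who have a Pap test instead are set to none here.

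| F (assumed) | Form only | Known status | Status missing | Apparent participation |
|---|---|---|---|---|
| 0% | 0 | 1,400 | 80% | 1,400/1,400 = 100% |
| 2% | 140 | 1,540 | 78% | 1,400/1,540 = 91% |
| 5% | 350 | 1,750 | 75% | 1,400/1,750 = 80% |
| 10% | 700 | 2,100 | 70% | 1,400/2,100 = 67% |
| 40% | 2,800 | 4,200 | 40% | 1,400/4,200 = 33% |

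The last row is an extreme: every woman in the plan's assumed 30% hysterectomy and 10% pregnancy groups posts the form. P / (P + F) exceeds P whenever P + F is below 1, so each row overstates the true 20%.

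**Comparisons between categories.** Take two categories with true participation of 20% and 10%, and F = 2% in both. The apparent figures are 20/22 = 91% and 10/12 = 83%, so a twofold difference shrinks to a ratio of 1.09. Now take two categories that both truly participate at 20%, with F = 2% in one and 10% in the other. The apparent figures are 91% and 67%, a difference that is not there.

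**Adjusted proportions.** Data analysis also plans proportions with ineligible women removed. If the form-only returns come from ineligible women, they leave the denominator and the known-status figure returns to 1,400/1,400 = 100%. The overall adjusted figure also rises, but far less: at F = 5%, and before removing mail returned to sender, it is 1,400/(7,000 − 350) = 21%.

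**Pap arm.** There are 1,000 women per screening group. Take 5% participation, one of the Table 2 scenarios. Let a and b be the form-return shares among participants and non-participants; neither is given.

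Apparent participation = 0.05a / (0.05a + 0.95b)

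- a = 50%, b = 2%: 0.025/0.044 = 57%, from 44 forms.
- a = 10%, b = 10%: 0.005/0.100 = 5%, from 100 forms.
- a = 10%, b = 30%: 0.005/0.290 = 2%, from 290 forms.

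The Pap-arm figure is unbiased only when a = b and can err either way. The kit-arm figure is pushed upward. A contrast between the arms would mix the two selection effects.

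**Pap attenders in the kit arm.** Outcomes counts them as successes. They need not return a form, so they can be participants who are lost from these two subgroups.

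**The case against.** A reader might infer that kit-arm proportions must be near 100% by construction. The documents do not support that. Data collection lists posting the form back as a route of its own, apart from returning the kit. The form asks about hysterectomy and pregnancy, and the Exclusion criteria rely on women reporting such things after mail-out, so some non-participants will have known status. Under intention to treat they stay in the denominator. The figure is near 100% only if few such forms arrive, or in the adjusted proportions.

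A reader might also infer that no denominators exist at all. They exist among form-returners, but they are incomplete and selected. The under-screened women come from the registry database, and the article does not say whether it records these variables. The firm statement is about never-screened women.

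Other points have some weight:

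- No test or between-arm contrast by these factors is stated. That stands, though reporting proportions by arm invites the contrast.
- The comparison of participants with non-participants is limited to age and SES, which suggests that the authors saw the limit. It was not carried over to the list of participation subgroups.
- This is descriptive reporting outside the stated objectives, and an analysis plan may set rules for missing data. The first part limits the importance. The second does not remove the problem: the article itself says the forms make these analyses possible, and the data it describes do not supply the denominators for participation.

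**Conclusion.** The point holds. By the data sources described, participation by cultural background and Indigenous status cannot be calculated for all randomised women, most clearly in the never-screened group. What can be calculated overstates kit-arm participation: 67% to 100% against a true 20% for form-only return between 10% and 0%, and 33% even at the 40% extreme. The Pap-arm figure is selected by a different act, so the two cannot be compared.

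The sizes rest on the plan's 20%, on every returned kit carrying its form, on no Pap attenders in the kit arm, and on assumed form-return rates. The direction in the kit arm, on these assumptions, does not depend on the rate chosen.

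The primary comparison, the follow-up outcome, and the subgroups by age, SES and time since last Pap test are unaffected. The change should be made, but it concerns secondary reporting.

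**What to change.** Take cultural background and Indigenous status out of the list of individual-level participation proportions in Data analysis. Report them as the make-up of participants with known status, by screening group and arm, with the number of participants whose status is missing in each arm. Amend the sentence in Interventions so that it promises a description of participants and not participation by these factors. If the registry does hold these variables for under-screened women, say so and state how complete they are; individual-level proportions could then be considered for that group.

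If participation by these factors is wanted, attach a Census area measure by postcode, such as the share of residents born overseas, speaking a language other than English at home, or Indigenous, and label it as area-level. Data analysis already assigns SES this way, and postcode is kept for non-participants.

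The first change costs only wording, and the second a further postcode merge. The drawback is that an area measure is ecological: it describes where a woman lives and does not give participation by her own background.
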